### Standard Protocol Items: Recommendations for Interventional Trials (SPIRIT)

This protocol has been written in accordance with the SPIRIT guidelines. The SPIRIT checklist is in Additional file 1.

## Discussion

Due to the introduction of ATRA and ATO, the outcome of patients with APL has dramatically improved over the last two decades. The APL0406 study showed the advantages of ATRA-ATO over ATRA-CHT in non-high-risk APL. In a clinical trial in China, a home-based treatment protocol with oral RIF plus ATRA was shown to be effective [11]. Medical costs and numbers of hospital days will be reduced [8]. However, the dosing schedules use of for arsenical agents were different in previous trials. Unlike in the APL0406 study, here, the arsenical agents and ATRA were used simultaneously for 2 weeks every 4 weeks. The simultaneous application of oral RIF and ATRA is more convenient for patients and may improve the efficacy [14].

The peak plasma arsenic after intravenous ATO may be several times greater than that of oral arsenical agents [15]. So, the patients may achieve molecular complete remission (MCR) quickly with ATO. In our trial, all the patients with APL will be treated with a combination of ATRA plus ATO during induction therapy.

Although the time to achieve HCR is about 30 days [16], the time to achieve MCR is different. In a clinical trial, the time to MCR ranges from 2 to 6 months [17]. However, in the recent major clinical trials, all of the patients received the same therapeutic courses in consolidation without considering the time to MCR. In this trial, patients will receive a total of six courses of ATRA-RIF or ATRA-ATO therapy after their PML-RARα is negative, which may result in a lower relapse rate.

Oral RIF is commercialized and commonly available in China. During remission therapy, the patients in the RIF group will be treated at home, while the patients in the ATO group will be treated in the hospital. Compared to intravenous ATO, RIF is relatively inexpensive and can be administered orally in outpatients. Thus, oral RIF may decrease the length of hospital stay and medical costs associated with APL treatment.

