**Methods:**

This study was designed as a multicenter, randomized controlled trial. The trial has a non-inferiority design with superiority being explored if non-inferiority is identified. All patients receive ATRA-ATO during the induction therapy. After achieving hematologic complete remission (HCR), patients were randomly assigned (1:1) to receive treatment with ATRA-RIF (experimental group) or ATRA-ATO (control group) as the consolidation therapy. During the consolidation therapy, the two groups receive ATRA plus RIF or intravenous ATO 2 weeks on and 2 to ~ 4 weeks off until molecular complete remission (MCR), then ATRA and oral RIF 2 weeks on and 2 to ~ 4 weeks off giving a total of six courses.

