### Consolidation therapy

#### ATRA-RIF group

The ATRA-RIF group will receive ATRA 60 mg/day (20–45 mg/m^2^/day) plus oral RIF (60 mg/kg/day) 2 weeks on and 2 to ~ 4 weeks off, until PML-retinoic acid receptor alpha (RARα) is negative by reverse transcriptase-polymerase chain reaction (RT-PCR), then ATRA and oral RIF 2 weeks on and 2 to ~ 4 weeks off, giving a total of six courses.

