#### ATRA-ATO group

ATRA 60 mg/day (20–45 mg/m^2^/day) plus ATO (0.15 mg/kg/day) 2 weeks on and 2 to ~ 4 weeks off, until PML-RARα is negative by RT-PCR, then ATRA and ATO 2 weeks on and 2 to ~ 4 weeks off, giving a total of six courses.

The PML-RARα fusion gene will be detected by RT-PCR before every cycle of consolidation therapy. The liver and kidney function, blood coagulation, electrocardiogram, arsenic concentration in blood and urine will be checked at least once a week during the whole treatment.

Regarding management of differentiation syndrome (DS) for the two groups: the hydroxyurea should be given at the earliest manifestations of suspected DS and hyperleukocytosis. At the same time, intravenously administered dexamethasone is administered at a dose of 10 mg every 12 h until the disappearance of signs and symptoms for a minimum of 3 days. The ATRA can still be given, but the dose of ATRA should be reduced by as much as half the conventional dose.

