### Monitoring

#### Follow-up monitoring

We will monitor bone marrow samples by PCR every 3 months after finishing the consolidation therapy to detect molecular relapse. The sustained observation will last for 2 years. If the PML-RARα gene expression is positive, PCR will be repeated for confirmation within 4 weeks. If the PML-RARα gene expression is negative, the patients need to proceed to consolidation therapy or conversely the patient needs to be treated for relapse.

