#### Relapse is defined as follow [12]:

Hematologic relapse is defined by bone marrow blasts of 5%, reappearance of blasts in the blood, or development of extramedullary disease. Molecular relapse: if studied pre-treatment it is defined by recurrence of minimal residual disease (MRD) as assessed by quantitative RT-qPCR or by multi-color flow cytometry.

The secondary outcomes of this trial are hospitalization days and medical costs in the two arms. The medical costs will be calculated for each patient. The hospitalization costs for induction and consolidation therapy will be calculated for inpatients. The hospital costs for induction therapy and consolidation therapy will be calculated for outpatients. All medical costs can be collected and multiplied by the unit cost of each resource use. After the patient is discharged from the hospital, we can obtain the medical costs from the medical record in hospital according to the patient’s name/case number. For the outpatients, the medical costs can be obtained from the outpatient system after the patient’s visit. Hospitalization days will be recorded over a 10-month time frame.

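### The number of consolidation courses and the control arm's drug after molecular remission are stated inconsistently, and the 10-month hospitalisation window is sure to cover all treatment on only one reading

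*Protocol article*

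**What the plan says.** **Number of courses.** In the protocol article, the abstract (Methods) has both groups treated up to MCR and then given ATRA with oral RIF on the same on-off schedule, to a total of six. The ATRA-RIF group section treats until PML-RARα is negative, "then ATRA and oral RIF 2 weeks on and 2 to ~ 4 weeks off, giving a total of six courses". The ATRA-ATO group section has the same structure: "then ATRA and ATO 2 weeks on and 2 to ~ 4 weeks off, giving a total of six courses". The Discussion says that "patients will receive a total of six courses of ATRA-RIF or ATRA-ATO therapy after their PML-RARα is negative". It gives this as a reason to expect fewer relapses, and contrasts it with trials that gave every patient the same courses whatever the time to MCR.

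**Drug after MCR in the control group.** The abstract sentence covers both groups and names oral RIF. The ATRA-ATO group section names ATO.

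**PCR-negative patients in follow-up.** Follow-up monitoring describes three-monthly PCR after consolidation has finished, with a repeat test after a positive result. It then says: "If the PML-RARα gene expression is negative, the patients need to proceed to consolidation therapy".

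**Hospital days.** The secondary outcomes are hospitalisation days and medical costs. For the first, "Hospitalization days will be recorded over a 10-month time frame"; no start is given. Costs are tied to induction and consolidation, with no limit in months.

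**Time to MCR.** The Discussion reports that in a cited trial "the time to MCR ranges from 2 to 6 months".

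**The concern.** Two centres could give different numbers of courses, and different drugs after MCR in the control arm, and each could point to the protocol in support. Post-consolidation monitoring begins when consolidation ends, so its start moves with the unresolved length.

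The hospital-day outcome depends on the same question. The Discussion says RIF patients are treated at home during remission therapy and ATO patients in hospital. If treatment runs past the recording window, the days lost are therefore mainly control-arm inpatient days. Reducing hospital days is a stated study hypothesis, and truncation would shrink the measured difference. Days and costs would also cover different periods for the same patient.

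**Working it through.** **Inputs**
- Cycle: 2 weeks on and 2 to 4 weeks off, so 28 to 42 days (Consolidation therapy). The Discussion describes a 4-week cycle.
- Induction: about 30 days to hematologic remission (Discussion).
- Time to MCR: 2 to 6 months (Discussion, from a cited trial). Assumption: counted from the start of induction.
- PCR before every consolidation cycle (ATRA-ATO group).
- Window: 10 months (Outcome measures). Assumption: counted from the start of induction; randomisation is tried as an alternative.
- 30.44 days per month, so 10 months = 304.4 days and 6 months = 182.6 days.

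The article does not derive the 10 months. The figure can be compared with the schedule but not reproduced.

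**Length of six courses, to the last dose** = 5 × cycle + 14 days
- 4-week cycles: 5 × 28 + 14 = 154 days = 5.06 months
- 6-week cycles: 5 × 42 + 14 = 224 days = 7.36 months

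**Reading A, six courses in total** = 30 days + six courses
- (30 + 154)/30.44 = 6.0 months; (30 + 224)/30.44 = 8.3 months
- With the last rest period: (30 + 168)/30.44 = 6.5 and (30 + 252)/30.44 = 9.3 months

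All of these lie inside 10 months.

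**Reading B, six courses after MCR** = time to MCR + six courses. Months to the last dose:

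| MCR at (months) | 2 | 3 | 4 | 5 | 6 |
|---|---|---|---|---|---|
| 4-week cycles | 7.1 | 8.1 | 9.1 | 10.1 | 11.1 |
| 6-week cycles | 9.4 | 10.4 | 11.4 | 12.4 | 13.4 |

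If MCR is recognised only at the next pre-cycle PCR, the ranges are 7.9 to 11.6 and 9.7 to 13.9 months. The total is then 8 to 12 courses (4-week cycles) or 7 to 10 (6-week cycles), against 6 under reading A.

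**Latest MCR that still fits the window**
- Window from induction: 10 − 5.06 = 4.9 months; 10 − 7.36 = 2.6 months
- Window from randomisation (about 1 month later): 5.9 and 3.6 months

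**ATO days lost with MCR at 6 months, control arm still on ATO.** The window leaves 304.4 − 182.6 = 121.8 days after MCR.
- 4-week cycles: the fifth course runs over days 112 to 126 and loses about 4 days. The sixth is lost whole (14). Total about 18.
- 6-week cycles: courses four to six start on days 126, 168 and 210, so 3 × 14 = 42 days are lost.

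These are 18 and 42 of the 84 post-MCR treatment days. With MCR recognised only at pre-cycle PCR, the loss is 28 of 168 consolidation ATO days (17%) with 4-week cycles and 42 of 140 (30%) with 6-week cycles.

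If the window starts at randomisation, 151.8 days remain after MCR. The loss falls to about 2 days (4-week cycles; the sixth course runs over days 140 to 154) or 28 days (6-week cycles; courses five and six).

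**If the abstract governs the drug after MCR**, the late courses are oral RIF in both arms. No ATO inpatient days are then lost, but the arms differ in arsenical only up to MCR.

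**The case against.** A reader might infer that the 10-month window fits only the shorter reading and that control-arm days will be cut off. The documents do not support that. With six courses after MCR and 4-week cycles, patients reaching MCR at 2, 3 or 4 months finish at 7.1, 8.1 and 9.1 months. Only later responders overrun, and the article gives no distribution of time to MCR from which to count them. The 2 to 6 months comes from another trial. If the window starts at randomisation, truncation nearly disappears with 4-week cycles.

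The Methods wording is also ambiguous rather than flatly opposed to the Discussion. The regimen in each arm's section is the same before and after PCR negativity, so six courses could be meant as six after MCR. On that reading the text agrees with the Discussion, and the window problem arises. On the six-in-total reading the window is adequate, and the Discussion is in conflict. The two difficulties are alternatives and do not add up.

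The loss of inpatient days also needs the ATRA-ATO section to prevail over the abstract on the drug after MCR. Truncation would work against the trial's own hypothesis, and it touches a secondary outcome. A fixed, equal window is a legitimate choice.

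All of this stands and limits the claim. It does not remove the need for one number of courses and one post-MCR drug per arm. Nor does it settle the follow-up rule: even if that sentence refers to the repeat test, consolidation has already finished by then.

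**Conclusion.** The inconsistency holds on the text alone and needs no assumption. It covers the number of courses, the control arm's drug after MCR, and the action for a PCR-negative patient in follow-up. This review takes no view on which statement is right.

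The consequence for hospital days is conditional. The 10-month window is sure to cover all planned treatment only if six courses are given in total. With six after MCR, treatment ends at about 7.1 to 13.4 months from the start of induction. If the MCR clock starts at hematologic remission instead, about 1 month is added.

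Where patients overrun and controls remain on in-hospital ATO, the hospital-day difference is understated. The loss is up to about 18 days (4-week cycles) or 42 days (6-week cycles) for a control patient reaching MCR at 6 months, and none for early responders. The average effect cannot be derived from the document. The point deserves correction because it affects the treatment given and a stated secondary outcome.

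**What to change.** 1. Reconcile the abstract, both arms' consolidation sections, Follow-up monitoring and the Discussion. They should give one number of courses (saying whether it is counted from randomisation or from MCR), one post-MCR regimen per arm, and one rule for a PCR-negative patient in follow-up. The choice belongs to the investigators.
2. State when the hospitalisation window starts, and make it long enough in both arms to cover the last protocol consolidation course. A fixed window common to both arms can be kept. If six courses after MCR is what is meant, the figures above point to at least 14 months from the start of induction.
3. Use the same period for hospital days and costs. Keep the induction costs that Outcome measures already includes, and report the consolidation (post-randomisation) part separately. Starting the cost window at randomisation would drop induction and change the defined outcome.

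The cost is a protocol amendment and slightly longer extraction for late finishers, from hospital records already used for the cost outcome.

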## Trial status

Recruitment commenced in July 2016 and the trial is scheduled to end in May 2020.

## Abbreviations

APL: Acute promyelocytic leukemia
ATO: Arsenic trioxide
ATRA: All-trans retinoic acid
CI: Confidence interval
CRF: Case report form
DFS: Disease-free survival
DS: differentiation syndrome
HCR: Hematologic complete remission
MCR: Molecular complete remission
PML: Promyelocytic leukemia
QoL: Quality of life
RARα: Retinoic acid receptor alpha
RARα: Retinoic acid receptor alpha
RIF: Realgar-indigo naturalis formula
RT-PCR: Reverse transcriptase-polymerase chain reaction
